## Outcomes, data collection, and management

### Outcomes {16}, plans for assessment, and collection of outcomes {25a}

After data collection at baseline, participants will return for outcome assessments at 12 weeks, 24 weeks, and 12 months. Details of the time point for outcomes and trial instruments are specified in each outcome below. All research assistants who are involved in data collection will be trained the correct use of instruments (e.g., ABPM) and questionnaires, as well as retrieval of data. After each assessment, the files will be reviewed to identify missing or erroneous data. Any missing information will be retrieved immediately from the instruments and the study participants.

### Primary outcome: daytime SBP assessed via ABPM at 24 weeks (immediate post-intervention)

Mean SBP will be the primary outcome since it is more predictive of cardiovascular outcomes than DBP, especially in older adults [33]. WatchBP O3 (by Microlife) is a validated and recommended ABPM monitor by multiple international societies (available at https://www.stridebp.org/bp-monitors) and will thus be used in this trial. ABPM will be conducted on recruitment and at 12 weeks, 24 weeks (primary study endpoint), and 12 months. IRT session will be separated from ABPM measurement by at least 24 h [34]. ABPM will measure the BP every 30 min [35]. The actual sleep time will be estimated by a sleep diary, which is the preferred method as shown in our previous research and by international recommendations [36]. The methods for conducting ABPM (including the use of the non-dominant arm and appropriate cuff size) and the definition of a valid ABPM report will be in accordance with the latest European Society of Hypertension ABPM measurement guidelines [37]. Our prior research experience showed that patient adherence to repeated ABPMs can be poor because sleep may be affected by ABPM in some patients. Therefore, although wearing the ABPM monitor for at least 24 h will be encouraged, ABPM will be performed only during waking hours in reluctant patients whose sleep is affected [37]. This will not affect our primary outcome.

### Secondary outcomes

Other ABPM parameters, which also predict cardiovascular outcomes, will be our secondary outcomes and include mean daytime SBPs at other time-points (i.e., 12 weeks and 12 months), mean daytime DBP, mean nocturnal SBP/DBP, mean 24-h SBP/DBP, BP dipping status, and BP variability (by average real variability as recommended by systematic review) at all time-points (12 weeks, 24 weeks, and 12 months) [38].

### Carotid–femoral pulse wave velocity

Carotid–femoral pulse wave velocity (cfPWV) and pulse waves will be analyzed by applanation tonometry using SphygmoCor (AtCor Medical Pty Ltd.) with the accompanying SphygmoCor Software Suite (SphygmoCor System). SphygmoCor is the most well-validated device for measuring PWV [39]. The measurements will be obtained with the patient in a supine position after at least 5 min of resting, and the cfPWV will be recorded sequentially at the carotid and femoral artery. Although aortic PWV (aPWV) was suggested by the research council for another project, cfPWV measurement is recommended by international guidelines and the device for measuring aPWV (Mobil-O-Graph [IEM, Germany]) is not available in Hong Kong [23]. PWV is the gold standard for measuring large artery stiffness, is reversible after short-term interventions (e.g., 6–12 weeks), is an independent predictor of cardiovascular events, and has also been reduced after aerobic endurance exercise and low-to-moderate intensity resistance exercise training [40, 41]. cfPWV will be measured on recruitment and at 24 weeks and 12 months.

### FMD of brachial artery

The test is widely used clinically to assess endothelial function (i.e., endothelium-dependent vasodilation) in human as described previously [42–45]. In brief, FMD will be performed using a high-resolution linear array transducer (L10-5), with a median frequency of 7.5 MHz and a standard Sonosite System (model MicroMaxx, Bothell, USA). The brachial artery diameter will be measured manually, with due attentions of reproducibility, coefficient of variation, and a stringent FMD protocol, according to international guidelines (e.g., in a quiet, temperature-controlled room, subject lying supine, refraining from ingesting caffeine) [46, 47]. The longitudinal image of brachial artery is obtained 5–10 cm above the elbow. After a qualified image is acquired for analysis, a pressure cuff placed distal to the imaging probe at the forearm will be inflated to 50 mmHg above the SBP for 5 min. The longitudinal image of the brachial artery is scanned continuously for 3 min after the deflation of the cuff (reactive hyperemia). The percentage change in peak brachial artery diameter before and after the cuff inflation will be calculated and reported as the FMD of the subject. Due to budget constraints, FMD measurement cannot be provided to all participants. Instead, FMD measurement will be performed by a blinded senior sonographer with full training and practical sonographic experience for over 30 years [43–45], in a subsample of patients in the intervention group (*n* = 50) and in the control group (*n* = 50). FMD measurement will be conducted at baseline, 24 weeks, and 12 months.

### Patient safety

The safety of IRT is currently underreported in RCTs [4]. Therefore, adverse events (including emergency department visits and hospitalizations) and the number of FMC and private clinic visits, as well as the incidence of falls, musculoskeletal injuries, new-onset stroke, ischemic heart diseases (including angina and myocardial infarction), heart failure, renal failure, and deaths, will be self-reported and retrieved from the HK Hospital Authority computerized medical system (CMS). These will be monitored throughout the trial and at the last data collection endpoint (i.e., 12 months).

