## Introduction

### Background and rationale {9a}

Hypertension (HT) is the most prevalent chronic condition and is the leading cause of cardiovascular and renal morbidity and mortality [1]. Despite effective treatments, only approximately one-third of patients with HT have optimal control of their blood pressure (BP) [1]. Although anti-HT medications can effectively reduce BP, patients’ non-compliance to medications is prevalent globally (~ 40%), due to misconceptions (e.g., medications can cause renal damage) and psychosocial factors (e.g., forgetfulness) [2]. Similarly, patients have poor adherence to the effective aerobic and dynamic resistance exercises because additional time, skills, training venue, and equipment are required [3]. Conversely, isometric resistance exercise training (IRT), involving low intensity, sustained isometric exercise, can overcome these barriers because they are safe, time efficient (approximately 14 min per session, 3 sessions per week), easy to learn, and require little to no equipment [4]. Isometric exercise involves a muscle contraction with no change in muscle length and joint angle, contrasting with dynamic resistance exercise which involves repeated muscle shortening and lengthening. In clinical practice and research, the two most well-studied and well-structured IRT are the wall squat and hand grip exercise [4, 5]. Furthermore, when compared with other types of exercise, IRT carry no joint impact (lower risk of joint injury), have lower myocardial oxygen demand (less chest pain or ventricular arrhythmias and more suitable for patients with cardiovascular diseases), and require less space (more suitable for patients living or working in crowded areas or with limited mobility) [6, 7]. The latest 2023 network meta-analysis also found IRT most effective to reduce office BP (by ~ 8/4 mmHg) among all exercise modalities (e.g., aerobic/resistance training) in reducing office BP (by ~ 8/4 mmHg) [8].

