### Eligibility criteria for participants {14a}

Patients meeting all these criteria will be included: (i) a suboptimal daytime SBP of > 135–160 mmHg on a 24-h ABPM (the internationally recommended cut-off for elevated BP, the rationale for focusing on SBP is explained under “Outcomes”) [12]; (ii) reported no regular physical activity or less than that recommended for adults by the World Health Organization (e.g. < 150 min of moderate-intensity aerobic exercise per week); (iii) on stable doses of anti-HT medication(s) for ≥ 4 weeks if the patient is receiving drug treatments; (iv) agree for no drug changes during the intervention period (24 weeks); and (iv) aged ≥ 18 years old. Patients receiving or not receiving anti-HT drugs will be included to maximize external validity and investigate responders’ characteristics. Only patients with mildly elevated daytime SBP of > 135–160 will be included to ensure safety as drug changes are avoided as far as possible during the 24-week intervention period. Patients will be excluded if any of the following criteria are met: (i) cannot provide informed consent; (ii) unwillingness to repeat ABPM (primary outcome); (iii) relative contraindications to ABPM (i.e., diagnosed atrial fibrillation, night-time workers, occupational drivers, or patients with bleeding tendencies); (iv) severe osteoarthritis pending knee replacement surgery (these patients may be unable to perform the IRT (i.e., wall squat exercise)); (v) known secondary HT; (vi) use of ≥ 3 anti-HT medications at maximum doses or ≥ 4 anti-HT medications (these patients have resistant HT and represent another disease spectrum); (vii) SBP or Diastolic BP (DBP) are > 160 mmHg or > 100 mmHg, respectively, on ABPM at baseline or at 12 weeks follow-up to ensure safety (these patients require early treatment); (viii) pregnancy/breastfeeding; and (ix) active malignancy (Table 1).

**Table 1 Tab1:** Inclusion and exclusion criteria

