#### Harms {17}

There are no anticipated risks associated with the wall squat and stretching exercises, as these interventions have been found to be safe, and adverse events are rare [4]. However, if any suspected or actual complications arise, participants are instructed to seek medical assistance, including attending the accident and emergency unit (access is not limited by current trial), and to contact the study team at their earliest convenience. As part of adherence monitoring, all participants already have the contact information for the research team. Any hospitalizations will be promptly reported to the relevant ethics committee within 24 h, or as soon as possible.

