### Baseline data collection

Data on age, sex, ethnicity, educational status, household income, marital status, smoking status (current smoker, ex-smoker, or never smoked), work status, family history of cardiovascular diseases and HT, and comorbidities (such as diabetes mellitus, hyperlipidemia, cardiovascular diseases [e.g., stroke, ischemic heart disease, heart failure], and chronic kidney disease) will be collected using the CMS and by self-reporting. Alcohol use will be assessed by the validated Alcohol Use Disorders Identification Test [52].

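### The new-onset limit on the named stroke count, and arguably on the heart and renal counts, does not fit a trial that admits patients who already have these diseases

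*Protocol article*

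**What the plan says.** The Patient safety section of the protocol article sets out three kinds of safety data, taken from self-report and the public hospital record system and followed to 12 months:

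- a general line: "adverse events (including emergency department visits and hospitalizations) and the number of FMC and private clinic visits";
- the incidence of falls and musculoskeletal injuries;
- within the same incidence list, "new-onset stroke, ischemic heart diseases (including angina and myocardial infarction), heart failure, renal failure, and deaths".

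Only the last group carries the word new-onset, and it appears once, directly before stroke.

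On who can enter, Eligibility criteria for participants {14a} and Table 1 give nine exclusions. Diagnosed atrial fibrillation is among them. Prior stroke, ischemic heart disease, heart failure and chronic kidney disease are not. Baseline data collection then records as comorbidities "cardiovascular diseases [e.g., stroke, ischemic heart disease, heart failure], and chronic kidney disease".

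**The concern.** An outcome limited to first onset suits a population free of the disease at entry. This trial expects some participants who are not. If the qualifier is applied as written, a participant with an earlier stroke who has another one during the programme may not be counted under stroke. If it also governs the rest of the list, the same holds for recurrent infarction, decompensation of known heart failure and worsening of existing renal failure.

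This matters for a stated aim. Objectives {10} includes the safety and tolerability of the exercise, and both the introduction and the Patient safety section say that earlier trials under-reported safety. The rationale also presents isometric training as "more suitable for patients with cardiovascular diseases". Participants with such disease are the ones whose experience bears on that statement, and a first-onset count cannot register recurrence or worsening of the condition they already have. The Discussion plans longer follow-up for cardiovascular events and a pooled individual-patient analysis, so an unclear definition could carry forward.

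**Working it through.** The documents contain no figure to reproduce on this point. They give no prevalence of prior cardiovascular or renal disease and no event rates. The check is a reading of the text.

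**Step 1: can such patients enter?** Yes. None of the nine exclusions removes them, and the baseline form asks for exactly these conditions.

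**Step 2: how far does new-onset reach?** Two readings are open.

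- *Narrow:* it qualifies stroke only. In support, it is written once and cannot sensibly extend to deaths at the end of the list, so nothing forces it onto the items between.
- *Wide:* it qualifies stroke, ischemic heart disease, heart failure and renal failure. In support, these follow as one run of diseases after the adjective, and the incidence of a chronic state ordinarily means new cases.

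**Step 3: apply both readings to events in participants with a history.**

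| Event during the trial | Narrow reading | Wide reading | General adverse event line |
|---|---|---|---|
| Recurrent stroke | can be left out | can be left out | within scope |
| Second infarction | counted, if incidence means events in the trial | can be left out | within scope |
| Decompensation of known heart failure | no rule given | can be left out | within scope |
| Worsening of existing renal failure | no rule given | can be left out | within scope |
| Chronic kidney disease progressing to renal failure | counted | counted, since renal failure is new | within scope |
| First stroke in a participant with prior angina | counted | counted | within scope |

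Stroke is affected on both readings, unless new-onset is taken to mean any new stroke event; the text does not say so. The other three diseases are affected on the wide reading. On the narrow one, worsening of a chronic condition still has no coding rule, so two assessors could classify the same event differently.

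**Step 4: what catches the events left out?** The general line has no new-onset limit. In addition, Harms {17} states: "Any hospitalizations will be promptly reported to the relevant ethics committee within 24 h, or as soon as possible". Other cardiovascular risk factors provides serum creatinine and the urine albumin-to-creatinine ratio at baseline, 24 weeks and 12 months for everyone, so renal function is followed whatever the baseline disease. Research staff check safety at least every two weeks in the intervention arm, and the control arm receives the same contact.

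The gap therefore concerns where an event is counted, not whether it is collected.

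**The case against.** The strongest reply is that the qualifier is written only before stroke, that incidence may simply mean events occurring in the trial, and that the general adverse event line picks up everything else. The word including does not confine that line to emergency visits and admissions, so worsening managed in a clinic can also be an adverse event. The only safety test the article specifies, in Statistical methods {27a}, compares the overall proportion of participants with adverse effects by chi-square and is not restricted to new-onset disease. Most of this stands. It shows that recurrence and worsening remain in the safety data. It does not settle the disease-specific counts: a recurrent stroke may sit in an undifferentiated adverse event total and be absent from the line headed stroke.

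A second reply is that a journal article leaves event definitions to the full protocol or the analysis plan. That would answer a missing definition. Here a qualifier is stated, and it does not fit the article's own eligibility criteria.

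A reader might infer that the trial's safety outcome as a whole ignores worsening disease. The general line, the reporting of hospitalizations and the renal measurements contradict that.

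**Conclusion.** The point holds as a badly fitting definition in a list of named safety outcomes. Following the wording can leave recurrent stroke out of its count and, on a natural but not forced reading, recurrent infarction, decompensated heart failure and worsening renal failure out of theirs. This rests on two things that the text supports: patients with these diseases can be enrolled, and new-onset is taken in its ordinary sense of first occurrence.

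The size cannot be stated. A reader might try to calculate the share of events missed from assumed comorbidity and event rates. The documents supply neither, and pooling everyone with any prior disease would overstate the loss, because a participant with one condition can still have a first event of another type.

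A reader might also conclude that the cardiovascular comparison is biased towards showing no harm. The documents do not support this. They specify no test of the named cardiovascular counts, both arms share the same definition, and leaving out these events would dilute a difference only if harm were concentrated in participants with prior disease, on which the documents are silent. What is lost is information under the disease headings. The primary outcome and the sample size are unaffected.

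**What to change.** In Patient safety, replace new-onset with new, recurrent or worsening, and make clear that this applies to stroke, ischemic heart disease, heart failure and renal failure alike. For each of the four, report per arm the number of participants with at least one such event, marking whether the condition was present at baseline.

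The self-report, the hospital record retrieval and the baseline comorbidity data are already planned, so no new collection is needed. Some events will need a check against baseline status, and worsening calls for more judgement than first onset. The change needs an amendment through the ethics committee and an update of the registry record, as Protocol amendments {31} provides. Trial status reports 190 of 390 participants recruited, so it can still be made well before analysis, and events in those already enrolled can be classified from the same sources.

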### Other cardiovascular risk factors

These are important parameters for predicting future cardiovascular events and deaths and will be monitored at baseline, 24 weeks, and 12 months. These include fasting serum glucose, glycosylated hemoglobin, fasting serum lipid profile (total cholesterol, high-density and low-density lipoproteins, and total triglycerides), serum creatinine, and spot urine albumin-to-creatinine ratio.

### Covariates that affect BP

Patients may change their behavior, knowing about their suboptimal BP. Physical activities will be monitored by smart watch above. Other lifestyle changes were assessed by validated methods. For instance, (i) sleep quality and duration as measured by the validated Pittsburgh Sleep Quality Index questionnaire; (ii) physical activity level and sitting time duration, by the validated International Physical Activities Questionnaire (short form); (iii) diet and medication adherence (if on anti-HT medications), by the medication (9 questions) and diet (9 questions) domains of the Treatment Adherence Questionnaire for Patients with Hypertension; and (iv) stress level, by the Perceived Stress Questionnaire [48–51]. Overweight and obesity will be evaluated by body mass index (body weight/height2) and waist circumference measurements. Anti-HT drug use data will be retrieved from the CMS (or self-reported if patient follow-up is not conducted in public clinics). These will be measured at baseline, 12 weeks, 24 weeks, and 12 months. Furthermore, sodium and potassium intake will be assessed by 24-h urine collection at baseline and 24 weeks (primary end-point).

### Baseline data collection

Data on age, sex, ethnicity, educational status, household income, marital status, smoking status (current smoker, ex-smoker, or never smoked), work status, family history of cardiovascular diseases and HT, and comorbidities (such as diabetes mellitus, hyperlipidemia, cardiovascular diseases [e.g., stroke, ischemic heart disease, heart failure], and chronic kidney disease) will be collected using the CMS and by self-reporting. Alcohol use will be assessed by the validated Alcohol Use Disorders Identification Test [52].

### Plans to promote participant retention and complete follow-up {25b}

Participants are given supermarket coupons after they completed data collection at each timepoints (i.e., baseline, 12 weeks, 24 weeks, and 12 months) to reinforce participant adherence to the trial and data collection. Also, regular communication will be maintained with participants to promote adherence to the trial and complete follow-up. Data of participants at all timepoints will be collected even after the withdrawal of the interventions, with their consents. For participants who discontinue the trial, reasons for withdrawal will be obtained.

### Data management {26}

The data will be entered into the computerized database weekly or bi-weekly, depending on the recruitment rate. Data entries will undergo a double-checking process by two independent assessors to ensure accuracy and reliability. Each participant will be assigned a unique identification code for research data management. The code list can only be accessed by the research team and will be securely maintained by the principal investigator after the study is completed. All data are securely stored in password-locked computers and locked cabinet. Personal information will remain confidential throughout the study and will not be disclosed in future publications.

### Confidentiality {33}

The confidentiality of sensitive data (i.e., personal information) will be ensured by minimizing the number of personnel who handles subject data. Data will also be kept in an encrypted folder, accessible only to the research team. Participant records will be stored in a locked cabinet. To further ensure confidentiality, each participant in the study will be assigned a unique identifying number for monitoring throughout the trial.

### Who will be included in each analysis {27b}

All randomized participants will be included in the analysis.

### How missing data will be handled in the analysis {27c} and methods for additional analyses (e.g. subgroup analyses) {27d}

In our funding proposal, we initially stated that “the analysis will be conducted on an intention-to-treat basis (primary analysis) and a per-protocol basis (sensitivity analysis).” However, per the European Medicines Agency (ICH E9[R1]), these terms can be ambiguous, and relevant estimands should be employed [53]. In this RCT, we anticipate intercurrent events (ICEs) such as changes in medications during the first 24 weeks, non-adherence to interventions, severe illnesses that prohibit participants to perform exercises (as described above), and switches between intervention groups. For our primary analysis, we will utilize the “treatment policy” estimand, which treats the occurrence of ICEs as irrelevant and uses the actual observed values for the outcome variable [53]. This approach aligns with our previous intention-to-treat analysis. For our secondary analysis, we will adopt the “hypothetical strategy” estimand, which estimates outcomes assuming all patients in their respective groups adhere perfectly to the interventions [53]. Additionally, missing data will be addressed through multiple imputation [54, 55].

